#### **11.2.4. Serious Adverse Events for Brazil**

An SAE is defined as any untoward medical occurrence that:

- Results in death
- Is life-threatening
- Requires inpatient hospitalization or prolongation of existing hospitalization
- Results in persistent or significant disability/incapacity
- Is an important medical event that may not be immediately life-threatening or result in death or hospitalization but may jeopardize the patient or may require intervention to prevent one of the other outcomes listed in the definition above

All AEs that are recorded will have their severity graded.

#### **11.2.5. Treatment of Overdose for Brazil**

Overdose of experimental regimens should be managed according to the labeling information (see appendices)

Risks from overdose from placebo pills are expected to be minimal.

#### **11.2.6. Safety Assessments for Brazil**

Safety will be assessed via participant Surveys, as shown in the SoA.

Participants will be asked to complete Surveys (Daily Survey and Exit Contact Survey) that include questions about their health, healthcare seeking, symptoms, illness within their household, contact, and mobility. Qualifying events will be recorded on the eCRF and reported as AEs, as described in [Section 10.3](#)

All AEs that are recorded must have their severity graded. To grade AEs, sites should refer to the DAIDS AE Grading Table, corrected Version 2.1, July 2017, which can be found on the DAIDS Regulatory Support Center website at [https://rsc.tech-res.com/docs/default-source/safety/division-of-aids-\(daids\)-table-for-grading-the-severity-of-adult-and-pediatric-adverse-events-corrected-v-2-1.pdf](https://rsc.tech-res.com/docs/default-source/safety/division-of-aids-(daids)-table-for-grading-the-severity-of-adult-and-pediatric-adverse-events-corrected-v-2-1.pdf).

## **12. Statistical Considerations**

### **12.1. Sample Size Determination for Brazil**

The sample size for Brazil of 492 patients per arm has been chosen for each experimental group to achieve 90% power with 0.05 two-sided Type 1 error for a pairwise comparison against the control (ascorbic acid) to detect minimum treatment efficacy defined by 27.5 % relative risk reduction (RRR) of preventing hospitalization assuming a control event rate (CER) of 20%.

The table below shows the sample size required at various treatment effects, CER, and drop-out rates for operating characteristics of 90% statistical power and two-sided type I error rate of 5%. Power may be lower depending on CER and drop-out rate (Table 1). As the initial sample size target, 165 per arm has been initially chosen for each experimental group to achieve 90% power with 0.05 two-sided Type 1 error for a pairwise comparison against the control (ascorbic acid) to detect at least 50% treatment efficacy in reducing the progression to LRTI (primary endpoint) assuming a CER of 30% and 5% drop-out rate.

**Table 1 Sample Size Per Arm Required to Detect a Relative Risk Reduction of 40% to 60% Under Various Control Event and Drop-out Rates**

| RR
R | Drop-out rate = 0% |             |             | Drop-out rate = 5% |             |             | Drop-out rate = 20% |             |             |
|---------|--------------------|-------------|-------------|--------------------|-------------|-------------|---------------------|-------------|-------------|
|         | CER=1
0%        | CER=2
0% | CER=3
0% | CER=1
0%        | CER=2
0% | CER=3
0% | CER=1
0%         | CER=2
0% | CER=3
0% |
| 40
% | 962                | 437         | 261         | 1013               | 460         | 275         | 1202                | 546         | 327         |
| 50
% | 578                | 263         | 158         | 609                | 277         | 165  | 723                 | 329         | 198         |
| 60
% | 375                | 171         | 103         | 395                | 180         | 108         | 469                 | 214         | 128         |

**Acronyms:** CER: Control event rate; RRR: Relative risk reduction.

Sample size calculation was done with the desired operating characteristics of 90% statistical power and 5% type I error rate (two-sided).

As illustrated in the table above, the statistical power will depend heavily on the observed CER. Given uncertainty of the target population, the final target sample size will be re-estimated after four weeks after the first patient is randomized using the observed CER and drop-out rate in the control group as a blinded sample size re-assessment. As it is difficult to predict the enrollment rate, the recruitment rate will be assessed on a weekly basis starting at the end of second week.

The sample size for TOGETHER 3 was determined based on the sample size calculation for TOGETHER 1 (US trial). The initial sample size target for TOGETHER 1 is 165 patients per arm that will achieve 90% power with 0.05 two-sided Type 1 error for a pairwise comparison against the control group (ascorbic acid) to detect treatment effect of 50% relative risk reduction (RRR) in reducing the progression to LRTI (primary endpoint) assuming a control event rate (CER) of 30% and 5% drop-out rate.

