| 
Brazil
 
For evaluations of experimental interventions compared to control, a total of 492 persons per arm will be enrolled.
 
A second cohort of low-risk participants will not be enrolled in Brazil.
                                                                                                                                                                                                                                                                                                                                                                                                                                                                                                                                                                                                                                                                                                                                                                                                                                                                                                                                                                                                                                                                                                                                                                                                                                                                                                                                                                                                                                                                                                                                                                                                           |

|                                          |                 |
|------------------------------------------|-----------------|
| Date/version: May 19, 2020 – V1.0 | Page: 10 |
|------------------------------------------|-----------------|

| Harmonized protocol document                                                          |
|---------------------------------------------------------------------------------------|
| Short title: Outpatient Management of SARS-CoV-2 for High-Risk Adults in LMICs |

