**Sample size:**

In Brazil, 492 patients per arm for placebo, HCQ, and LPV/r to achieve 90% power with 0.05 two-sided Type 1 error for a pairwise comparison against the control (ascorbic acid) to detect minimum treatment efficacy defined by 27.5 % relative risk reduction (RRR) of preventing hospitalization assuming a control event rate (CER) of 20%. Eligible participants will be randomized at an equal allocation ratio to study experimental interventions or placebo. In Brazil, if other eligible patient(s) are in the same household, they may be assigned to different regimen.

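### 492 patients per arm gives about 63% power, not 90%, for a 27.5% relative risk reduction at a 20% control rate; 90% needs about 987 per arm

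*Protocol*

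**What the plan says.** Section 12.1 gives the basis for the Brazil sample size: "The sample size for Brazil of 492 patients per arm has been chosen for each experimental group to achieve 90% power". Each active arm is compared pairwise with control at a two-sided 5% level. The target effect is a "minimum treatment efficacy defined by 27.5 % relative risk reduction (RRR) of preventing hospitalization", and 20% of controls are expected to have the event. The Synopsis makes the same claim in its sample size paragraph: "492 patients per arm for placebo, HCQ, and LPV/r to achieve 90% power with 0.05 two-sided Type 1 error". The Synopsis population table repeats the number as the enrolment target ("a total of 492 persons per arm will be enrolled"), and Section 5.1 gives 492 per arm as the initial Brazil enrolment. No drop-out rate is stated for the 492.

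Table 1 in Section 12.1 lists sample sizes per arm for 90% power at two-sided 5%. It covers RRRs of 40%, 50% and 60%, CERs of 10%, 20% and 30%, and drop-out of 0%, 5% and 20%. The 27.5% scenario on which 492 rests is not in the table.

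**The concern.** With the CER fixed, the required sample size grows roughly with the inverse square of the effect. Table 1 needs 437 per arm for a 40% RRR at a CER of 20% with no drop-out. Scaling that by (40/27.5)² = 2.12 already gives about 925 per arm, before allowing for the larger variance in the treated arm. The protocol's figure is only 55 above 437.

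This is the headline power statement for the hospitalization outcome, which is part of the primary endpoint for Brazil in the Synopsis and Section 4.1. If it is wrong, a drug with exactly the minimum effect of interest would be missed far more often than the protocol says. Anyone judging the design or a non-significant result by the stated 90% would be misled.

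**Working it through.** **Inputs**
- Control rate p1 = 0.20 (Synopsis; Section 12.1).
- RRR 27.5%, so p2 = 0.20 × (1 − 0.275) = 0.145 and the difference is 0.055.
- Two-sided alpha 0.05 (z = 1.960) and power 90% (z = 1.282).
- Equal allocation (Section 7.4).
- No drop-out, since none is stated for 492. This is the case most favourable to the plan.

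**Step 1. Identify the protocol's formula from Table 1.**
Unpooled two-proportion formula: n per arm = (1.960 + 1.282)² × [p1(1 − p1) + p2(1 − p2)] / (p1 − p2)².

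| RRR | CER 10%: formula / Table 1 | CER 20%: formula / Table 1 | CER 30%: formula / Table 1 |
|---|---|---|---|
| 40% | 961.4 / 962 | 436.1 / 437 | 260.9 / 261 |
| 50% | 577.9 / 578 | 262.7 / 263 | 157.6 / 158 |
| 60% | 374.8 / 375 | 170.5 / 171 | 102.4 / 103 |

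Rounded up, the formula returns all nine no-drop-out cells.

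**Step 2. Apply the same formula to the Brazil scenario.**
Variance term: 0.20 × 0.80 + 0.145 × 0.855 = 0.160 + 0.123975 = 0.283975.
n = 10.507 × 0.283975 / 0.055² = 986.4, so **987 per arm**. With 5% drop-out: 987 / 0.95 = 1,039.

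Other standard methods agree on the size: arcsine 986, pooled variance 990, log relative risk 1,006, pooled with continuity correction 1,026.

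**Step 3. Power at 492 per arm.**
Power = Φ(0.055 / √(0.283975/492) − 1.960) = Φ(2.289 − 1.960) = Φ(0.329) = **62.9%**.

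| Drop-out | Evaluable per arm | Power |
|---|---|---|
| 0% | 492 | 62.9% |
| 5% | 467 | 60.7% |
| 20% | 394 | 53.5% |

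The pooled-variance version gives 62.7% at 492. A simulation of the uncorrected chi-square test (400,000 trials) gives 63.0%.

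**Step 4. Does another reading of the inputs return 492?**
The same formula at a 27.5% RRR and a CER of 20% gives:
- two-sided 5%, 80% power: 737 per arm;
- one-sided 5%, 90% power: 804 per arm;
- one-sided 5%, 80% power: 581 per arm.

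None is near 492. It corresponds to 90% power in either of two other scenarios: an RRR of about 38% at a CER of 20% (about 39% with 5% drop-out), or a 27.5% RRR at a CER of about 34%.

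Twice 492 is 984, almost the required per-arm number. A per-arm figure may have been taken as the two-arm total, but the protocol does not say so and the conclusion does not depend on it.

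**The case against.** Three points can be made for the plan.

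**The actual analysis may do better than a plain two-proportion test.** Section 12.3.1 plans covariate adjustment and the use of all placebo participants, with borrowing of past and possibly external control data. Section 3 says US control data may be used. So 63% is the power of the pairwise comparison as stated, not necessarily of the final analysis. That qualification stands, but it does not rescue the figure. Neither the Synopsis nor Section 12.1 bases 492 on borrowing or adjustment. Doubling the effective controls to 984 at no penalty gives Φ(0.055 / √(0.160/984 + 0.123975/492) − 1.960) = 77%. Even unlimited controls give only about 93%.

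**The number is provisional.** Section 5.1 calls 492 the initial enrolment, and Sections 5.1 and 12.1 plan a blinded re-assessment. Section 5.1 ties an increase to a lower CER or higher drop-out than expected. If the CER is 20% as assumed, neither condition corrects the starting error. Rerunning the formula from scratch might expose it, but a possible later change does not make the present statement true.

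**Section 12.1 warns that power may fall with the CER and drop-out.** The shortfall here occurs at exactly the assumed CER and with no drop-out at all.

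**Conclusion.** The power statement is wrong as written. For the pairwise comparison that the protocol describes, 492 per arm gives about 63% power against the stated 90%, so the type II error is 37% against 10%. The sample size that matches the stated inputs is 987 per arm before drop-out, twice the figure given.

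This rests on the protocol's own inputs, equal allocation, an unadjusted two-proportion comparison and no drop-out; any drop-out lowers the power further. The result does not depend on the choice of formula, because every standard method tried gives between 986 and 1,026 per arm. The protocol does not show which of the four figures (492, 27.5%, 20% or 90%) was entered wrongly.

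**What to change.** First trace where 492 came from. If the RRR or the CER was mistyped, correct that input and show the calculation.

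Otherwise restate the design property in the Synopsis (Sample size) and in Section 12.1: 492 per arm gives about 63% power (61% with 5% drop-out) for a 27.5% RRR at a CER of 20%, and 90% power for an RRR of about 38% (39% with 5% drop-out), for an unadjusted pairwise comparison at two-sided 5%. State the drop-out rate assumed for 492. Rows for 27.5% and 38% in Table 1 would let the reader check the claim but are optional. This is a text change only. It leaves enrolment as it is, and the stated property becomes less favourable.

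If the sponsor wants to keep 90% power for a 27.5% RRR at a CER of 20%, the number must read 987 per arm (1,039 with 5% drop-out) in the Synopsis and in Sections 5.1 and 12.1. For three arms before drop-out, that raises enrolment from 3 × 492 = 1,476 to 3 × 987 = 2,961. The correction does not require this.

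Either way, Sections 3, 5.2 and 12.1 also give 165 per arm as an initial target, and that figure has to be reconciled separately.

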## 12.2. *Populations for Analyses*

For analysis purposes, the following populations are defined and will be described in greater detail in the trial Statistical Analysis Plan:

| Population               | Description                                                                                                                                                                                |
|--------------------------|--------------------------------------------------------------------------------------------------------------------------------------------------------------------------------------------|
| Intention to Treat (ITT) | All enrolled participants who are randomized into the study: high-risk group for the primary clinical endpoint; high- and low-risk groups (separately) for the primary virologic endpoint. |
| Safety population        | All subjects who received at least 1 dose of study medication                                                                                                                              |
| PK evaluable             | Participants from the DBS Sub-study with at least 1 interpretable PK sample                                                                                                                |

DBS: dried blood spot; PK: pharmacokinetic;

## 12.3. *Statistical Analyses*

The Statistical Analysis Plan will be developed and finalized before database lock and will describe the participant populations to be included in the analyses, the detailed analytical plans

| Harmonized protocol document                                                          |
|---------------------------------------------------------------------------------------|
| Short title: Outpatient Management of SARS-CoV-2 for High-Risk Adults in LMICs |

with endpoints and procedures for accounting for missing, unused, and spurious data. An Interim Monitoring Plan will also be developed to describe approaches for re-estimation of sample size and any planned interim analyses. This section presents a brief summary of the planned statistical analyses of the primary and secondary endpoints (these are listed in [Section 0](#)).

### **12.3.1. Efficacy Analyses**

Demographic characteristics (age, sex, race) of each study group will be tabulated.

The mean age (plus range and standard deviation) by sex of the enrolled participants, as a whole and per group, will be calculated.

#### **Primary analyses:**

The primary analyses will be conducted on the ITT population overall and by cohort. Participants randomized to each active arm will be compared to participants randomized to placebo (ascorbic acid). The primary analysis will make use of all participants randomized to placebo, whether contemporaneously enrolled or not using an Empirical Bayesian information borrowing method (described below). Due to anticipated heterogeneity in risk of disease progression, pre-specified baseline variables, including age, weight, and days of symptoms at time of enrollment will be included in the model to increase precision.

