**Drug interactions between study arms and rifampicin-treated and ART treated patients:** We included an explicit exclusion criteria to exclude patients with potentially clinically significant pharmacokinetic and pharmacodynamic drug interactions as determined by the study clinical pharmacologist. As far as possible, we want to study HIV-positive and patients treated for pulmonary tuberculosis as they are potentially a high risk for severe disease who could benefit from an early treatment. If one of the study experimental drugs are considered to put the patient at increased risk due to drug interactions, randomization for such patients will be limited to the study arms that are deemed to be safe by the study clinical pharmacologist.

**Misclassification as low-risk:** We thoroughly question participants about their medical history to best as possible correctly classify them as high- or low-risk for co-morbidities. We will also request participants for consent to access their medical records to review for co-morbidities.

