22. Taking chronic medications associated with prolonged QT and may induce Torsades de Pointes as per CredibleMeds.org, including certain antipsychotic medications or antidepressants (e.g., citalopram, venlafaxine, and bupropion) and unable to stop during the trial
23. Baseline QTc interval of > 470 ms in males, and > 480 ms in females
24. Potentially clinically significant pharmacokinetic and pharmacodynamic drug interactions as determined by the study clinical pharmacologist\*\*
25. Pregnancy or lactating women

Note:

\*Patients who have already started on the assigned therapy may stop treatment if they test negative for SARS-COV-2 during screening

\*\* If randomization to one study arm may be considered to put the patient at increased risk due to drug interactions, randomization will be limited to the arms with safer interventions. This is important to allow participation of HIV-infected participants on treatment and rifampicin-treated participants.

|                                          |                 |
|------------------------------------------|-----------------|
| Date/version: May 19, 2020 – V1.0 | Page: 27 |
|------------------------------------------|-----------------|

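### Patients barred from one drug are randomised among the other arms only, yet each drug is compared with all placebo patients, including those who could never have received it

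*Protocol*

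**What the plan says.** Two rules meet here.

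- **Restricted randomisation.** For patients in whom one study drug raises an interaction risk, section 3.3 says that "randomization for such patients will be limited to the study arms that are deemed to be safe by the study clinical pharmacologist". Note ** to exclusion criterion 24 in section 6.1.2 repeats the rule and gives its purpose: "This is important to allow participation of HIV-infected participants on treatment and rifampicin-treated participants". On HIV-positive patients and those treated for pulmonary tuberculosis, section 3.3 adds that "they are potentially a high risk for severe disease who could benefit from an early treatment".
- **Unrestricted controls.** Section 12.3.1 compares each active arm with placebo in the ITT population, and says: "The primary analysis will make use of all participants randomized to placebo, whether contemporaneously enrolled or not". Section 12.2 defines one ITT population for the whole trial: "All enrolled participants who are randomized into the study: high-risk group for the primary clinical endpoint". It does not define one for each comparison.

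Neither account of the stratification uses arm eligibility: section 7.4 names site and risk level, and the synopsis names time since symptom onset and age. The covariates named in section 12.3.1 are age, weight and days of symptoms. The borrowing method in the same section deals with past and external controls, not with patients who had fewer arms open to them.

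**The concern.** A patient barred from LPV/r can enter only HCQ or placebo. Such patients are therefore present in the placebo group and absent from the LPV/r arm. Under equal allocation they are also over-represented on placebo, because they are shared between two arms instead of three. The imbalance comes from the assignment rule, so a larger sample does not remove it. If barred patients have a different event risk from the rest, the placebo rate shifts and the drug's estimated effect shifts with it.

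The effect may travel further. Section 5.1.1 plans to use the HCQ and LPV/r effects against placebo as an empirical prior for the combination arm.

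**Working it through.** **Inputs from the protocol:** three arms with equal allocation (sections 5.1 and 7.4); 492 per arm, control event rate 20%, relative risk reduction 27.5%, that is 0.200 against 0.145, at two-sided 5% (section 12.1).

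**Assumptions, because the protocol gives no figure:** share f of all randomised patients barred from drug A, 2% to 20%; event risk of barred patients k times that of the others, 1.0 to 2.0; eligible patients have a 20% risk; drug A has no effect.

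**The plan's own figure.** A standard two-proportion calculation for 0.200 against 0.145 with 90% power gives 990 per arm, not 492; with 492 per arm the power is 62.7%. That is a separate matter and does not bear on this point. Here 492 serves only as the size of the placebo arm.

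**Step 1: barred share of placebo.** Barred patients go 1:1 to placebo and the other drug; the rest go 1:1:1. So w = (f/2) / (f/2 + (1−f)/3). For f = 10%: 0.05 / (0.05 + 0.30) = 14.3%. The share in drug A's arm is 0%.

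**Step 2: apparent effect of an inert drug.** Placebo rate = 0.20(1−w) + 0.20kw, and apparent RR = 0.20 / placebo rate. For f = 10%, k = 1.5: 0.20 × 0.857 + 0.30 × 0.143 = 0.2143, and RR = 0.20 / 0.2143 = 0.933.

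**Step 3: type I error.** Unadjusted two-sided normal test at 1.96, with 492 on placebo and 492(1−w) on drug A.

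| Barred (f) | Share of placebo (w) | RR, k = 1.0 | RR, k = 1.5 | RR, k = 2.0 | Type I error, k = 1.5 | Type I error, k = 2.0 |
|---|---|---|---|---|---|---|
| 2% | 3.0% | 1.000 | 0.985 | 0.971 | 5.2% | 5.6% |
| 5% | 7.3% | 1.000 | 0.965 | 0.932 | 5.9% | 8.6% |
| 10% | 14.3% | 1.000 | 0.933 | 0.875 | 8.2% | 18.1% |
| 20% | 27.3% | 1.000 | 0.880 | 0.786 | 15.7% | 46.0% |

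At k = 1.0 the type I error stays at 5.0% throughout.

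**Step 4: after restricting controls.** Both groups then consist only of patients who could have been assigned either arm, so the apparent RR equals the true RR, leaving aside any non-concurrent borrowing. Controls that remain are 492(1−w): about 477, 456, 422 and 358. With that many in each arm, power for 0.200 against 0.145 is 61.4%, 59.4%, 56.2% and 49.5%, against 62.7% with 492 in both arms.

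**The case against.** The strongest reply is that the sentence in section 12.3.1 is about calendar time: the word all is qualified by concurrent and non-concurrent enrolment and by the borrowing method. Sections 12.2 and 12.3 leave the detail of the analysis populations to the SAP, and the covariate list is introduced as open-ended. An SAP could therefore restrict controls or adjust for eligibility. This has weight, but as written the control set is every placebo patient, and the protocol does not require the permitted arms to be recorded before randomisation. The clinical pharmacologist's judgement would be hard to reconstruct afterwards for placebo patients.

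The objections to size and direction stand:

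- A reader might infer that the placebo rate is certainly raised and that the drug will look better than it is. The protocol does not support this. Every Brazilian participant already needs a risk factor, no low-risk cohort is enrolled there, and section 3.3 does not say that barred patients are at higher risk than the other participants. Among the section 6.1.1 risk factors, HIV appears through a low CD4 count, not through being on treatment.
- A reader might take 10% or 20% barred as the expected case. No figure in the protocol supports either. Exclusion criteria 7, 9 to 11, 16 and 22 already remove many users of interacting or QT-prolonging drugs from every arm, so the group left may be small.
- The error rates above come from an unadjusted test, whereas the plan is to adjust for covariates.

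**Conclusion.** The defect holds as a matter of design. Followed as written, the protocol places controls with zero probability of receiving a drug in that drug's primary comparison. Its consequence cannot be sized from the protocol. Over the assumed ranges it runs from nothing (equal risk), through negligible (RR 0.985 at 2% barred and 1.5 times the risk) and appreciable (0.93 at 10% and 1.5 times), to serious (0.79 at 20% and double risk). These are unadjusted figures for an inert drug at a 20% eligible risk and equal allocation. The likelier direction favours the drug, because section 3.3 describes these patients as potentially high risk, but that is a likelihood and not a finding.

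**What to change.** 1. Have the IWRS record, before randomisation, the set of arms each patient may receive.
2. In section 12.3.1, state that each active arm is compared only with placebo patients who were eligible to be randomised to that arm, with the comparison stratified by or adjusted for the eligibility set. Apply the same restriction to borrowed placebo data. Stratifying the randomisation itself by eligibility set is optional.
3. Reconcile exclusion criterion 24, which reads as an exclusion from the trial, with its note **, which admits the same patients to some arms.

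The cost is one data field, a sentence in the analysis section, and fewer controls in the affected comparison: of 492, about 15 are lost at 2% barred, 36 at 5% and 70 at 10%. The loss of power is small if few are barred. It grows with the barred share: at 20% about 134 controls would go. Part of the fall in power shown above is not caused by the fix, because drug A's arm is smaller in any case when barred patients cannot enter it.
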